## Materials and methods

### Study design

This study will be a parallel-designed, two-armed, pilot randomized control trial (RCT) determining and comparing the feasibility and user-perceived acceptability of a personalized management program (IMP and PPSP) and conventional program (informal peer debrief) in critical care healthcare professionals. It will also determine the preliminary effectiveness of improving wellbeing, work engagement, and decreasing burnout symptoms. After baseline screening questionnaires are completed, eligible participants will be randomized into one of two groups in a 1:1 ration. This protocol was prepared in accordance with the SPIRIT guidelines (Fig 1 and S1 Table). Flinders University (ref. number: 4703) and University of Southern Queensland (ref. number: H22REA178) Human Research Ethics Committee approved the study (S2 Table). The study was also registered under the Australian and New Zealand Clinical Trials Registry (ACTRN12622000749707p). Fig 2 demonstrates the study flowchart.

**Fig 1 pone.0285038.g001:**
[figure not shown]
SPIRIT schedule of enrolment, interventions, and assessments. *IMP will run for 2 weeks (blue arrow), PPSP debrief will run for the following 6 weeks (black arrow), IMP, Individualized Management Plan; PPSP, Professional Problem-Solving Peer; IES-R, Impact of Event Scale-Revised, CD-RISC, Connor-Davidson Resilience Scale 25; TIS, Attrition Turnover Inventory; MBI, Maslach Burnout Inventory; PES, Practice Environment Scale; DASS-21, Depression, Anxiety, and Stress Scale-21; PSI, Problem Solving Inventory; PANAS, Positive and Negative Affect Schedule.

**Fig 2 pone.0285038.g002:**
[figure not shown]
Study flowchart.

### Study setting

The study center will be located at the College of Nursing and Health Sciences, Flinders University. Study data will be collected through online questionnaires using Qualtrics [34] and virtual sessions (IMP, debrief, and feedback semi-structured interviews) using Zoom Video Communications [35].

### Eligibility criteria

Critical care professionals who are interested to participate will register their interest in an electronic form. The form will contain the Impact of Event Scale-Revised (IES-R), which will be used to assess their eligibility prior to completing and signing the electronic informed consent form. The eligibility criteria will include (a) registered healthcare professionals practicing within an Australian or New Zealand critical care setting (i.e., Physicians, Nurses, Allied Health) and (b) have access to a personal computer or device with camera and microphone. The trial will also include individuals that are either undertaking or not undertaking prescribed treatments for mental health conditions. The exclusion criteria will include (a) individuals that are under any type of work compensation claims, (b) have contradictions to any of the interventions, and (c) are considered as ‘high risk’ of self-harm or psychological harm, which will be determined at the recruitment phase using the Impact of Event Scale-Revised (IES-R) [36]. Potential participants scoring 37 or more on the IES-R will be excluded, as this demonstrates a score that is high enough to suppress the individual’s system’s functioning, requiring referral for professional support [36, 37]. Participants that score 37 and above will be contacted by the research team and offered a one-on-one consult with a clinical psychologist, where they will be on-referred to an employee assistance program or their general practice for further professional support.

### Intervention

#### Intervention group

The intervention group will receive an Individualized Management Plan (IMP) and Professional Problem-Solving Peer (PPSP) debrief. The IMP is a 30-minute, virtual, once-off, one-to-one consult with a psychologist. The psychologist will provide tailored, immediate, and simple strategies within the session as their usual scope of practice (using clinical judgement). These strategies will be centered around the participant’s everyday living, for example, recommendations for improved sleeping habits, encourage development of exercise habits, and methods for relaxation. Participants will be advised by the psychologist to implement these strategies into their daily lives. The list of semi-structured questions can be found in Table 1.

**Table 1 pone.0285038.t001:** IMP semi-structured questions.

Themes	Guiding Questions
General Questions	How are you feeling?
	How are you finding your job at the moment? Are there any stressors that you are currently experiencing?
Mental Health	Can you tell me about any times over the past few months/weeks that you’ve been bothered by low feelings, stress, or sadness?
Physical Health	Has it affected your sleeping habits? Have you noticed any changed? Difficulty sleeping? Restlessness?
	How would you describe your appetite over the past weeks? Have your eating habits changed in any way?
Autonomy, choice, and control	How often during the past months/weeks have you felt as though your moods, or your life, were under control?
Relationships and belonging	Describe how ‘supported’ you feel by others around you—friends, family or otherwise
Self-perception	Let’s talk about how often you have felt satisfied with yourself over the past months/weeks.
Hope and hopelessness	Can you tell me about your hopes and dreams for the future? What feelings have you had recently about working towards those goals?

This study will administer a professional peer debrief led by accredited peer support leader(s). It will include a semi-structured, 6-week, group-based, virtual, informal, peer debrief session. The peer debrief session aim to encourage social interactions and engagement between participants rather than to achieve structured debrief objectives, such as successful reflection. The objectives are weighted towards achieving peer support using informal structures of debrief. The peer debrief will also incorporate the theory of social problem-solving. The goal for peer debrief is to learn and apply problem-solving approaches [38]. The peer support leader will support participants to positively change problematic situations and/or provide techniques to decrease emotional distress from the afflicted problem [38]. This will be facilitated through group discussions, experience sharing, and individual guidance to summarize the causes of the problem, develop feasible goals and strategies, and perform analysis on the effects (success or failure) of the implemented strategy [38].

The purpose of integrating IMP was due to the key component of ‘tailoring’, which was identified in Adnan et al. (2022) refined program theory [32, 33]. Tailoring caters towards the individual’s experience, addressing contextual factors and mechanisms. It also facilitates understanding of the unique characteristics and experiences of the individual, which may allow investigators to address their individual’s needs, resources, preferences, and goals; ultimately giving meaning to the intervention, increasing personal relevance, and prioritizing the user’s control and involvement. Moreover, debrief facilitates the reflection of situations, exploring one’s thoughts, and questioning assumptions to achieve positive learning that is based on lived experiences [39]. An individual’s performance can also be revisited to enable greater understanding of the situation, foster critical thinking, and provide adjustments toward future situations [39].

#### Active control group

The informal peer debrief will include mutual support between participants with shared experiences. Like PPSP debrief, its goals are not to achieve debrief outcomes, rather, to encourage social interaction and engagement between participants—enabling a platform to discuss concerns, problems, and feelings [40]. The informal peer debrief will be a semi-structured, 6-week, group-based virtual, peer debrief intervention. Peer support leader(s) will conduct the sessions but will not provide active solutions. The list of semi-structured questions will be consistent in both intervention and control debrief groups with differences in the ‘Pre-briefing’, ‘Discovering’, and ‘Deepening’ sections; informal peer debrief will not include problem-solving approach (see Table 2).

**Table 2 pone.0285038.t002:** Debrief session layout.

Topic	Content
Introduction	• Introduction of the support leader and researcher present in the session • What this study is about and who is conducting the study
**Pre-briefing**	• Purpose of the debrief session and the role of the support leader in facilitating discussions and prompting self-reflection • Items that can be discussed (i.e., encounters/stressors at the workplace) • **Management of situations using problem-solving approaches and connecting new learnings into future situations.**
Defusing	• Encouraging participants to talk about how they feel when encountered with a stressful situation. • Allow reflection of their feelings and recapping the scenario
**Discovering**	• Allow other participants to reflect on the situation and provide their thoughts and ideas • Enable participants to explore any similar situations that they may have encountered. • **Support leader(s) may ask other participants on how they would approach the situation, their rationale, and potential future strategies. The support leader(s) can also offer their own mental model on problem-solving approaches to deal with the situation.**
**Deepening**	• **Reflection on what can be done in similar future situations.** • **Finding a relationship between the suggested strategy to other situations at work.**
Summary	• Recapping what was discussed in the session • Ending with one thing that can be taken away from the session and used in their workplace.

Note: The intervention group (PPSP debrief) will also use techniques stated in both ‘roman’ and ‘bold’ typeface, whereas the control group will follow techniques noted in ‘roman’ typeface only.

### Measurements

Participants will complete self-reported questionnaire measures at four timepoints: baseline (T0), after treatment (T2), 1-month follow-up (T3), and 3-months follow-up (T4). Qualitative journal entry will be completed throughout treatment (T1)—the journal entry will include reflective questions for participants complete. Participants will additionally provide sociodemographic characteristics at T0 and treatment feedback (both through an online questionnaire and demi-structured interviews) at T2. Examples of sociodemographic characteristics will include gender, age, living status, citizenship, employment, qualifications, and family responsibilities. Audits of study screening, enrolment logs, attendance list to the consult and debrief sessions (intervention and active control), and study records (completion of the assessment measures at the five assessment points) will also be conducted.

### Primary outcomes

#### Feasibility

Feasibility of the study will be assessed based on the recruitment process, enrolment, treatment delivery, and data collection. The audits of participants referred and attended the consults each week will be used to measure the recruitment and enrolment. Audits of completing questionnaires, journal entries, feedback questionnaires, and feedback semi-structured interviews will measure the feasibility of treatment delivery and data collection.

#### User-perceived acceptability

User-perceived acceptability will measure user intervention engagement and user satisfaction. Both outcomes will be measured using journal entries, treatment feedback questionnaire, and feedback semi-structured interviews. Journal entry question such as ‘What knowledge/strategies were you able/unable to implement from the debrief session?” will measure intervention user engagement. Treatment feedback questionnaire will be used to measure user satisfaction, which includes questions surrounding user experience, barriers, enablers, and likelihood of recommendation. This will be further supported by feedback semi-structured interviews, that will be conducted as a 30 minute, one-on-one, once-off session for each participant. The feedback semi-structured interviews aim to ask questions surrounding feasibility and user-perceived acceptability. The questions will include topics that cover benefits, improvements, and potential changes for the future larger study. Other secondary outcomes will be measured using questionnaire instruments described below.

### Secondary outcomes

The secondary measures are directed to determine the impact of the intervention. Secondary outcome measured using self-reported questionnaire instruments, treatment feedback questionnaire, feedback semi-structured interviews, and journal entry. The journal entry question on ‘I feel burned out’ will measure the participant’s perception on burnout. The treatment feedback questionnaire and feedback semi-structured interviews that addresses questions surrounding benefits of the intervention and changes in participant’s viewpoints measures the impact of the intervention.

#### The Utrecht Work Engagement Scale (UWES)

The UWES-9 is used to measure work engagement–assumed to be the opposite of burnout. It is a 9-item revised scale scored on a 7-point Likert scale from “Never” to “Always” [41].

#### Attrition Turnover Inventory (TIS)

The TIS scale is used to determine turnover intentions [42]. It is a 6 item scale scored on a five point Likert scale, between poles of intensity from 1 being never to 5 being always [42].

#### Maslach Burnout Inventory (MBI)

The MBI scale is the gold standard in measuring burnout [43]. It comprises of three scales of emotional exhaustion (9 items), depersonalization (5 items) and personal accomplishment (8 items). It is a 22-item instrument [43].

#### Practice Environment Scale (PES)

The PES is an instrument, which measures the practice environment, defined as factors that enhance the ability to practice skillfully and deliver high quality care [44].

#### Depression, Anxiety, and Stress Scale (DASS-21)

DASS-21 is a self-reporting scale that is designed to measure negative emotional states of stress, anxiety, and depression with seven subscales within each measure [45]. Scoring can be presented as total scores and scores for three subscales [45]. The subscales are further divided into five severity ranges including normal, mild, moderate, severe, and extremely severe [45].

#### Problem-Solving Inventory (PSI)

The PSI assess awareness and evaluates the individual’s problem-solving styles or abilities [46]. It is a self-reported measure consisting of 35 six-point Likert scale with three factors including problem-solving confidence, approach-avoidance style, and personal control [46]. Lower scores demonstrate attitudes and behaviors that are associated with successful problem solving [46].

#### Positive and Negative Affect Schedule (PANAS)

The PANAS measures positive and negative affect using 20-items; 10 negative affect markers, and 10 positive affect markers [47]. The items are rated on a scale from one being ‘very slightly or not at all’, to five being ‘extremely’ [47].

### Sample size estimation

To achieve the primary aims of determining feasibility and acceptability, a pragmatic approach will be taken in that if sufficient data to address the secondary aim (preliminary effectiveness) can be achieved, this should also be sufficient for the primary aim. Power calculations were therefore conducted to determine the sample size required for the secondary aim of this study.. Analyses variance with repeated measures between and within the design in relation to the participants wellbeing was used, with low effect size estimated (η^2^ = 0.061). Significance level was 0.05 and power at 0.95. This resulted to a minimum sample of 106 participants for the study, having considered 20% attrition rate. The sample size was rounded off to 110 participants (55 each group) to enable equal samples sizes in both groups.

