This study will combine the three concepts of peer support, problem-solving and tailoring to determine its effectiveness in improving wellbeing and engagement and decreasing burnout amongst critical care healthcare professionals. To the authors’ knowledge, there are no similar studies with the proposed intervention within the critical care workforce. Thus, the primary aim of this study is to test the feasibility and user-perceived acceptability of a combined Individual Management Plan (IMP) and Professional Problem-Solving Peer (PPSP) debrief in comparison to informal peer debrief. Specifically, the study will test the feasibility of the recruitment process, enrolment, intervention delivery, data collection, and completion of assessment measures in a sample of critical care healthcare professionals. User-perceived acceptability will be assessed using participant engagement to the intervention and user satisfaction. The secondary aim is to examine the preliminary effectiveness of the intervention on improving wellbeing, work engagement, and decreasing burnout. This study hypothesizes that the combined intervention will be (1) feasible (in terms of recruitment, enrolment, intervention delivery, and data collection, and completion of assessment measures), (2) acceptable in terms of participant engagement and user satisfaction, and (3) effective in improving wellbeing, engagement, and decreasing burnout symptoms than the informal peer debrief intervention at post-treatment and at the two follow-up periods (1 month and 3 months).

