This protocol provides information on a randomized control trial that plans to carry out the intervention based on the combination of tailoring the intervention, peer support, and problem-solving approach on critical care healthcare professionals. The lack of evidence on the feasibility and acceptability of such concepts requires a pilot study to gain greater insight into the preparation process. It is expected that the participants assigned to the intervention group will demonstrate feasibility and user-perceived acceptability of the treatment processes, alongside statistically significant better results in improving wellbeing, work engagement, and decreasing burnout components. The outcomes in this study will be used as preliminary data for the larger and more defined randomized control trial.

One strength identified in this protocol is the inclusion of a large sample size, which is a result from the estimation of the sample size calculations. This provides an opportunity to acquire more accurate mean values, provides smaller margin or error, and identify outliers that may be present (in skewing the data) within smaller samples [52]. The use of randomization, controlled, and the use of two follow-up timepoints in the design of this study may also provide understanding of both immediate and early longitudinal patterns and outcomes of treatment changes of the intervention. A limitation of the study includes the use of an active control intervention, rather than the use of a waitlist control design. Active controls have ethical advantages as it allows the provision of care to participants that are seeking help and enables non-intervention evaluation. However, such designs may produce overestimates of the intervention’s effects and that having an active control counteract and minimize such aspects. Despite this, a greater understanding of the feasibility and acceptability of combining IMP and PPSP debrief is essential to foster a larger study that determines its effectiveness in improving wellbeing, work engagement, and decrease burnout symptoms for critical care healthcare professionals.

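### The 95% power is claimed for an effect called low, but eta-squared 0.061 is a medium effect, and the figure fits an overall group-by-time test, not each visit

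*Protocol article*

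**What the plan says.** The Sample size estimation section sizes the whole trial on the secondary aim of preliminary effectiveness. It names the method as "Analyses variance with repeated measures between and within the design in relation to the participants wellbeing was used" and the effect as "with low effect size estimated (η^2^ = 0.061"). It continues: "Significance level was 0.05 and power at 0.95. This resulted to a minimum sample of 106 participants for the study", a figure that already allows for 20% attrition. The number is then rounded to 110, or 55 per arm. The section does not say which effect of the repeated-measures ANOVA was powered, or what correlation between visits was assumed.

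The third hypothesis, at the end of the Introduction, is that the combined intervention does better than the "informal peer debrief intervention at post-treatment and at the two follow-up periods (1 month and 3 months"). The Planned analysis section examines longitudinal change and group differences with mixed linear models, and reports effect sizes for the changes T0–T2, T0–T3 and T0–T4. The Discussion expects statistically significant results and says: "One strength identified in this protocol is the inclusion of a large sample size".

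**The concern.** A reader who sees a low effect and 95% power will conclude that the trial can detect small differences, and that a null result would largely exclude them. The printed effect size does not support that, because 0.061 is not a small eta-squared. The two arms also share a six-week virtual group debrief run by peer support leaders. They differ by the problem-solving elements and one 30-minute consult, so whether half an SD is a modest assumption matters.

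The second issue is what the 95% refers to. The hypothesis and the planned effect sizes are laid out visit by visit, whereas a repeated-measures ANOVA calculation usually concerns an overall effect across visits. At stake is how a null or mixed result is interpreted and carried into the larger trial.

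**Working it through.** **Inputs.** From Sample size estimation: eta-squared 0.061, alpha 0.05, power 0.95, 20% attrition, 106 rounded to 110. From Measurements: four questionnaire timepoints, so m = 4. From Study design: two arms, 1:1. Completers: 110 × 0.8 = 88, or 44 per arm. The protocol gives no correlation ρ between visits; I assume equal correlations of 0.3, 0.5 and 0.7. Participants are treated as independent.

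**Effect size.** f² = 0.061/(1 − 0.061) = 0.0650, so f = 0.255. For two equal groups d = 2f = 0.51. By the usual convention f = 0.10 is small and 0.25 is medium. A small f = 0.10 would be an eta-squared of 0.01/1.01 = 0.0099, about one sixth of 0.061.

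**Reproducing the plan's figure.** Group-by-time F test with sphericity, noncentrality λ = N(m − 1)f², df = 3 and 3(N − 2):
- N = 90: λ = 90 × 3 × 0.0650 = 17.5, power 0.951.
- N = 88: λ = 17.2, power 0.947.
- N = 110: power 0.982.

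Adding 20% gives 90 × 1.2 = 108, or 88 × 1.2 = 105.6, against the stated 106. Dividing by 0.8 would give 90/0.8 = 112.5, that is 113, but 88 completers still have 0.947, so this is minor.

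Other routes fit less well. The same interaction with λ = N·m·f²/(1 − ρ) needs only 36 at ρ = 0.5. The group main effect, λ = N·m·f²/(1 + 3ρ), needs 128 at ρ = 0.5; with 88 completers it has 0.93, 0.85 and 0.77 at ρ = 0.3, 0.5 and 0.7.

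**A small effect on the test that fits.** With f = 0.10, λ = 88 × 3 × 0.01 = 2.64 and power is 0.24. With 110, λ = 3.30 and power is 0.30.

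**What 0.061 means if it is a partial eta-squared for group by time.** Suppose the group difference is 0 at T0 and δ at T2, T3 and T4. Its sum of squares about its mean is 0.75δ², so λ = (N/4)(0.75δ²)/(1 − ρ). Setting this equal to 3Nf² gives δ = 4f√(1 − ρ):

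| ρ | δ (SD) | Baseline-adjusted power at one visit, 88 completers | Change-from-baseline power |
|---|---|---|---|
| 0.3 | 0.85 | 0.99 | 0.92 |
| 0.5 | 0.72 | 0.97 | 0.92 |
| 0.7 | 0.56 | 0.95 | 0.92 |

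**What follows if the true difference is 0.51 SD.** Two-sided noncentral t at one visit, 44 per arm. The standardised difference is 0.51/√(1 − ρ²) with baseline adjustment and 0.51/√(2(1 − ρ)) for change from baseline. For the omnibus test, λ = (88/4) × 0.75 × 0.51²/(1 − ρ).

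| ρ | Baseline-adjusted | Change from baseline | Omnibus group by time, 0.51 SD at all three visits |
|---|---|---|---|
| 0.3 | 0.70 | 0.52 | 0.52 |
| 0.5 | 0.78 | 0.66 | 0.68 |
| 0.7 | 0.91 | 0.86 | 0.90 |

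**Precision.** The 95% CI half-width for an unadjusted difference at one visit, 44 per arm, is 1.96 × √(2/44) = 0.42 SD.

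**The case against.** The strongest defence is that the calculation works for the analysis the plan describes. A between-and-within repeated-measures ANOVA, followed by a mixed model of change over time, points naturally to group by time, and for that test 88 completers give 0.947. If 0.061 is that test's partial eta-squared, the implied shift also gives 0.95 to 0.99 at each visit with baseline adjustment. A baseline-adjusted average of the three later visits reaches 0.94 to 0.99 even at 0.51 SD. This stands. It rules out some stronger conclusions that a reader might draw:

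- That the 95% is simply false for the hypothesis under test. The protocol does not fix the test so narrowly, and the most natural one reproduces the figure.
- That the real power is 66%. That is an unadjusted comparison at a single visit with d = 0.51. Planned analysis specifies no such test, and it puts 0.061 on a different scale from the calculation that gives 106.
- That the trial must win at all three visits, with correspondingly low power. The Introduction lists the visits but states no such success rule.
- That the Discussion's sample-size strength must be withdrawn. It is argued from accuracy of means, margin of error and outliers, not from power.

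It is also fair that a condensed article may leave the correlation and the powered effect to a fuller document, and that efficacy is secondary here. But the defence does not rescue the word low. The reading that yields 95% implies a difference of 0.56 to 0.85 SD, which makes the label less apt.

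**Conclusion.** The effect label is wrong on the protocol's own number. Eta-squared 0.061 is medium: about 0.51 SD on the between-group scale, or 0.56 to 0.85 SD as a constant post-baseline shift if it belongs to group by time. The 95% is approximately right for an omnibus four-measure group-by-time test at that effect, and it should be read only so. For a small effect (f = 0.10) that test has 24% to 30% power.

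At 0.51 SD, visit-specific power with 88 completers is 0.70 to 0.91 baseline-adjusted and 0.52 to 0.86 for change from baseline. The effect-size conversion rests on no assumption beyond two equal groups. The visit-specific figures and the shifts rest on the assumed correlations of 0.3 to 0.7, equal correlation between visits, and independent participants. Severity is moderate: the primary aims are feasibility and acceptability, but the paragraph sets the size of the trial and governs how a null efficacy result will be read.

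**What to change.** Revise the Sample size estimation paragraph and leave the sample size at 110:

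1. Replace the low label with medium (f = 0.255, about half an SD or more).
2. State that 0.95 applies to the omnibus group-by-time test over four measures, and give the noncentrality convention and correlation assumption used.
3. Add the lower visit-specific power for the comparisons in the hypothesis and Planned analysis, or state the precision instead: a 95% CI half-width of about 0.42 SD at 44 per arm, unadjusted.
4. Do not claim or imply that small effects are detectable.

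The figure of 0.95 need not be removed, only attached to its test. The cost is a wording amendment with no added participants; the downside is that the stated sensitivity looks less favourable.
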